## Discussion

Providing bereavement care to relatives in the ICU is an important part of palliative care. Alongside a temporary disruption in their personal life, grief might have negative social and economic consequences as well, such as reduced time at work and decreased income. In today’s society and culture, talking about death is not always taken for granted. The added value of this research project is to improve psychosocial care for relatives during and after the death of their loved one. The newly developed multicomponent intervention may improve the bereavement process of the relatives; therefore, symptoms of complicated grief and related mental health problems of PICS-F such as depression, anxiety and posttraumatic stress, might decrease. While most bereaved relatives do not require bereavement support from a specialist (such as psychologist, psychiatrist), a considerable minority will benefit from non-specialized support (e.g., mutual help-groups) [49]. Identifying relatives at risk for mental health problems, will help to recognize the need for specialized support in an early stage. Another strength of the current study is the retrospective baseline measurement combined with a longitudinal prospective approach, thus collecting data in several timepoints to assess changes in mental health over time. These findings can inform ICU professionals on strategies to build an evidence-based guideline in bereavement services [32].

### Limitations and related risk strategies

This single-site study, based on the self-reported questionnaire answers of the respondents, may provoke bias in the results and limit generalizability. However, comparing the results with previous findings and international literature will minimize inappropriate conclusions. A stepped wedge or cluster randomized study could provide more general results, which is not the case in this study due to grant requirement of the institution. Another limitation may be difficulties with the implementation of multicomponent intervention. The adherence of the professionals may be influenced by workload pressure in clinical practice, insufficient knowledge, focus on high-tech and medical priorities, and their own vulnerability in delicate situations [50]. Moreover, ICU nurses may experience barriers in knowledge and competences in communication during the end-of-life situation [51]. Oncology nurses have built a broad expertise in the signs of complicated grief [52], which can provide a starting point to support the educational needs of ICU nurses [53].

Six strategies have been developed to stimulate the usage of the multicomponent intervention and limit the risk of non-adherence [31, 54–56]:
Educational sessions for all ICU nurses presenting the new tools and discussing communication strategies;Information strategies such as an informational pamphlet and reminders in a weekly newsletter;Champions in each ICU team, empowered by a two-day training in loss and bereavement care;Regular interactions between the investigators, the local champions and the team members to discuss difficulties;Including the nurse managers in advocating the bereavement tools if doomed necessary during daily start-up;Close collaboration with the department of Public Health and Erasmus MC University Medical Center, with extended expertise in this domain of palliative care and used practices among nurses and other allied healthcare providers.

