### Aim

The aims of the BRIC (Bereavement in Relatives in the Intensive Care) study for bereaved relatives of deceased ICU patients are: 1) to develop and implement a multicomponent nurse-led intervention, 2) to explore the experiences with bereavement care such as aspects of communication, quality of ding and death, and quality of support to relatives, 3) to determine the effectiveness of this intervention on complicated grief, anxiety, depression and posttraumatic stress and 4) to identify determinants and risk factors of complicated grief.

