### Methodology

This study protocol follows the Standard Protocol Items: Recommendations for Interventional Trials (SPIRIT) checklist [33]. The recommended schematic diagram detailing the schedule of enrolment, interventions and assessments is provided in Table 1. The study is non-blinded and non-randomized due to practical issues in the multicomponent intervention elements, which were applied intuitively and in a tailored fit to the relatives by ICU nurses.

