#### Study cohorts and time points

Both cohorts will be performed in study samples of 200 relatives per group, all participants will be invited to complete questionnaires measuring complicated grief, anxiety, depression and posttraumatic stress. Cohort 1 includes all reported first and second contact persons of patients who died in the ICU in 2018, which will serve as a pre-intervention baseline measurement. Eligible relatives were approached from March to May 2019 (−t_1_) and participants received the questionnaires directly after they signed the consent form (t_0_). The intervention was conducted from June 2019 onwards. Cohort 2, including all bereaved relatives in the ICU from October 2019 until March 2020, will serve as a post-intervention follow-up measurement. Eligible relatives will be approached 12 weeks after the death of their loved one (−t_2_) and participants will receive the questionnaires directly (t_1_) and at 6 months (t_2_) after they signed the consent form. The study design and timeline is presented in Fig. 1. For each deceased patient, up to 3 relatives can be included in the study. This recruitment process has been shown feasible in a previous study [39].

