## Conclusion

An accurate assessment of the implementation process through the RE-AIM model, combined with a high degree of fidelity to the intervention, is critical to the reliability, validity, replicability, and scale-up of the results of an intervention research study. The findings and evaluation of this study will be used to design and conduct a future multicentre trial. Nurses from other ICUs and nurses of other subspecialties, such as cancer nursing, will be encouraged to implement the developed intervention and to study the effects gaining comparative data. Finally, guidelines will be developed for ICUs aiming to adequately deliver support to relatives during the process of dying and death.

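### The limitations section presents the missing concurrent control as a loss of generality, but intervention and calendar period are fully aliased, so aim 3 (effectiveness) claims more than the design supports

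*Protocol article*

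**What the plan says.** All references are to the protocol article.

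- **Aim.** The third aim is "to determine the effectiveness of this intervention on complicated grief, anxiety, depression and posttraumatic stress".
- **Study cohorts and time points.** The comparison is fixed by date of death: "Cohort 1 includes all reported first and second contact persons of patients who died in the ICU in 2018", against "Cohort 2, including all bereaved relatives in the ICU from October 2019 until March 2020". Between the two, "The intervention was conducted from June 2019 onwards".
- **Methodology.** "The study is non-blinded and non-randomized due to practical issues in the multicomponent intervention elements".
- **Limitations and related risk strategies.** The study could be biased and less generalisable because it has one site and self-reported answers; setting the results beside earlier literature is offered as the safeguard. On alternative designs: "A stepped wedge or cluster randomized study could provide more general results". They were not used because of a grant requirement.
- **Abstract (Methods), Table 2 (Efficacy row) and Statistical analysis.** The before-after comparison is to be corrected for covariates. The covariates named are reason of admission, severity of illness, cause of death, bereavement care, time to say goodbye and social support.
- **Conclusion.** The findings are to feed a future multicentre trial, other units are to be encouraged to adopt and study the intervention, and finally "guidelines will be developed for ICUs aiming to adequately deliver support to relatives".

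**The concern.** What a stepped wedge or cluster randomised design mainly adds is concurrent controls: some relatives receive standard care while others, in the same months, receive the intervention. That is what allows a difference to be attributed to the intervention. Wider generality is a secondary gain. The limitations section states the secondary gain and leaves out the main one.

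At stake is the reading of the main result. If grief scores are lower in cohort 2, a reader who holds aim 3 beside the stated limitation will take the difference as an effect of the intervention that may not carry over to other hospitals. The design supports less than that: scores differed between two periods, and the intervention is one of the things that changed.

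**Working it through.** **1. The plan's own figure.** Statistical analysis states 200 relatives per group for d = 0.5, power 95%, two-sided .05, two-sample t-test. Normal approximation: n = 2(1.960 + 1.645)²/0.5² = 104 per group. The t-test needs 105 (power 0.9501). At 200 v 200 the power is 99.9%. So 200 is more than enough for its stated purpose, and this point does not rest on the sample size.

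**2. Overlap of the cohorts.** Control deaths cover January to December 2018 and exposed deaths October 2019 to March 2020. The overlap is 0 months. Nine months separate the close of the first window from the opening of the second, and their midpoints (1 July 2018 and 1 January 2020) are 18 months apart. In a model with an intercept, an intervention indicator and a period indicator, the last two columns are identical, so the design matrix has rank 2 with 3 columns. The two effects cannot be estimated separately at any sample size.

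**3. Whether the planned safeguards break the aliasing.**

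- *Covariate correction.* It can remove differences in measured patient and relative characteristics. It cannot remove changes in staffing, end-of-life practice or outside circumstances that are tied to period.
- *Repeated-measures ANOVA.* Statistical analysis makes pre- versus post-intervention a within-subject factor. Cohort 1 is measured once. Both measurements in cohort 2 follow implementation. No relative is seen in both periods, so there is no within-person control for trend.
- *Comparison with the literature.* This cannot show what changed inside this ICU. The article's own Background doubts that the large French study generalises to other countries, and says that the one Dutch ICU study of bereaved relatives known to the investigators did not measure complicated grief.

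**4. Illustration of size.** The document gives no figure for background change, so a range is assumed. With no intervention effect and a pure period shift of d SD, the two-sample t statistic has noncentrality δ = d·√(n₁n₂/(n₁+n₂)). At 200 v 200 this is 10d, that is 1, 2 and 3 for d = 0.1, 0.2 and 0.3. Rejection probability at two-sided .05 (noncentral t):

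| Relatives per group | 0.1 SD | 0.2 SD | 0.3 SD |
|---|---|---|---|
| 105 v 105 | 11% | 30% | 58% |
| 160 v 160 (see below) | 14.5% | 43% | 76% |
| 200 v 200 | 17% | 51% | 85% |

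The middle row allows for clustering: 1.5 relatives per death (Statistical analysis) and an assumed intracluster correlation of 0.5 give a design effect of 1 + 0.5 × 0.5 = 1.25, and 200/1.25 = 160. Recruiting more relatives raises the chance of a false attribution.

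**The case against.** The design is disclosed openly: the title and abstract call it pre-post, and the Methods say it is not randomised. Aliasing with period belongs to every uncontrolled before-after study, and the grant ruled out the alternatives. Much of the wording is cautious: the Discussion says the intervention may improve bereavement and that symptoms might decrease. This stands, and it makes the fault one of misstatement, not concealment. It does not correct aim 3 or the sentence on alternative designs.

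Five stronger readings are tempting, and the document does not support them.

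- *All change in case mix is counted as intervention effect.* It is not: correction for measured covariates is planned. What remains is unmeasured change tied to period.
- *The protocol admits no bias.* It does, for single site and self-report. The gap concerns the absent concurrent control.
- *The protocol goes straight to guidelines.* The Conclusion puts a multicentre trial first and guidelines last.
- *The trial's type I error is 17% to 85%.* Those figures rest on an assumed shift and on an unadjusted t-test. The planned hypothesis test is a repeated-measures ANOVA, and the regression is to allow for clustering.
- *Restricting cohort 1 to October to March deaths would isolate season.* Cohort 2 does cover only those months, against the whole year in cohort 1. But all of cohort 1 was approached in March to May 2019, so month of death fixes time since loss: about 11 to 17 months for January to March 2018 deaths and 2 to 8 months for October to December 2018 deaths, against an approach at 12 weeks in cohort 2. The restriction would exchange one imbalance for another.

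**Conclusion.** The point holds in a bounded form. Intervention and calendar period are fully aliased in this single-ICU comparison. The limitations section gives the cost of forgoing a stepped wedge or cluster randomised design as less general results, when the main cost is attribution. Aim 3 claims effectiveness; the design supports an adjusted difference between the periods before and after implementation.

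The aliasing follows from the stated dates and needs no assumption. The size of any resulting error is unknown. The 17%, 51% and 85% at 200 v 200 show only what shifts of 0.1, 0.2 and 0.3 SD would do to a simple t-test if the intervention had no effect; the document neither gives nor implies such a shift. It should be corrected, because it changes what the trial can conclude and costs little.

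**What to change.** 1. In Limitations and related risk strategies, state that without a concurrent control the comparison cannot separate the intervention from other changes between 2018 and 2019-2020, and that this concerns internal validity as well as generalisability.
2. Reword aim 3 and the planned conclusion as an adjusted difference between the periods before and after implementation. Leave effectiveness to the multicentre trial that the Conclusion already foresees.
3. In Statistical analysis, specify which covariates apply to the cohort comparison. Use patient variables that precede the intervention and are already extracted or named, such as age, gender, reason of admission, severity of illness and cause of death. Keep bereavement care and time to say goodbye out of this model: the intervention may change both, so adjusting for them could remove part of its effect. They can remain in the analysis of determinants.

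No new data and no change of design are needed. According to Study status, recruitment of cohort 2 had not yet started, so all three changes can precede any comparison of outcomes. The cost is a more modest claim.

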### Ethical considerations

This particular area of research, and some items in the questionnaires specifically, may be a confronting issue for participants. Bereaved relatives are vulnerable, and even voluntary participation in the study might evoke negative flashbacks of the ICU admission and death of their loved one. This possibility is taken into account by allowing the participants to share their own experience when completing the questionnaires. They choose what to reveal, and they are not required to answer. Previous studies have shown that comparable respondents usually characterize their participation as helpful and not harmful [57, 58]. Furthermore, information about supporting services such as contact with the research team, social work, and an independent medical specialist, is included in the participant information form and at the beginning of the survey. Those who express a need for support will be brought into contact with a social worker, a psychologist or their general practitioner (GP). The GP will be informed in advance on participation of their patient in the current study by an information letter. The study protocol is approved by the Medical Ethics Committee of Erasmus MC (MEC-2018-1598). Protocol modifications will be communicated to the study sponsor by email and to the Medical Ethics Committee by protocol amendment.

### Data dissemination

Public access to the study protocol, study details, participant-level dataset, and statistical code can be obtained from the correspondence author. The results will be disseminated to healthcare professionals, health services authorities and the public via presentations at national and international meetings and published in peer-reviewed journals. A lay summary of the results will be written and shared with the Dutch foundation FCIC and made available to participants on request.

## Conclusion

An accurate assessment of the implementation process through the RE-AIM model, combined with a high degree of fidelity to the intervention, is critical to the reliability, validity, replicability, and scale-up of the results of an intervention research study. The findings and evaluation of this study will be used to design and conduct a future multicentre trial. Nurses from other ICUs and nurses of other subspecialties, such as cancer nursing, will be encouraged to implement the developed intervention and to study the effects gaining comparative data. Finally, guidelines will be developed for ICUs aiming to adequately deliver support to relatives during the process of dying and death.

## Data Availability

Anonymized data gathered and analysed during the current study are not publicly available due to legal and ethical restriction. These can be requested from the corresponding author as well as text and photo material of the developed intervention.

## Abbreviations

ANOVA: Analysis of Variance
DSM-5: Diagnostic and Statistical Manual of Mental Disorders
FCIC: Family and patient Centered Intensive Care
GP: General Practitioner
HADS: Hospital Anxiety and Depression Scale
ICD-11: International Classification of Diseases
ICG: Inventory of Complicated Grief
ICU: Intensive Care Unit
IES-R: Impact of Event Scale-Revisited
TGI-SR: Traumatic Grief Inventory-Self Report Version
PICS-F: Post Intensive Care Syndrome Family
PIF: Participant Information Form
RE-AIM: Reach, Efficacy, Adoptation, Implementation and Maintenance
SPIRIT: Standard Protocol Items: Recommendations for Interventional Trials
